## Methods

ETNA-VTE-Europe is a single-arm, multinational, prospective, non-interventional PASS, which will be conducted across approximately 310 sites in 8 European countries (Austria, Belgium, Germany, Ireland, Italy, the Netherlands, Switzerland and the United Kingdom). The registry will enrol approximately 2700 patients with acute VTE treated with edoxaban, who will be followed over the 18 months subsequent to the index VTE. Approval from the responsible ethics committees and institutional review boards will be obtained prior to protocol implementation. Informed consent will be obtained from all patients prior to enrolment and compliance with the Declaration of Helsinki will be ensured throughout the study.

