### Objectives and outcome measures

The primary objective of ETNA-VTE-Europe is to quantify the long-term rate of VTE recurrence in a large, real-world population of acute symptomatic VTE patients prescribed edoxaban as part of their initial treatment regimen. Accordingly, the primary outcome measure will be the proportion of such patients who experience recurrent symptomatic VTE on one or more occasions within the 18 months following their index VTE, regardless of the length of edoxaban exposure.

The co-primary objective is to collect and evaluate real-world safety data regarding adverse drug reactions (ADRs) in patients treated with edoxaban across the currently approved indications. Therefore, ETNA-VTE-Europe data will be combined with 18-month safety data from the Edoxaban Treatment in routine cliNical PrActice for patients with non-valvular Atrial Fibrillation in Europe (ETNA-AF-Europe) study, a parallel European PASS evaluating the safety and effectiveness of edoxaban in real-world treatment of atrial fibrillation (AF) [10]. The outcome measure will be the proportion of patients who experience death (all-cause, cardiovascular, and VTE-related), bleeding events (major, clinically relevant non-major [CRNM], and minor bleeding; defined according to International Society on Thrombosis and Haemostasis [ISTH] criteria [11]), hepatic events, and/or other ADRs before the 18 month time-point in the two studies.

Secondary objectives are as follows: to evaluate the effects of persistent edoxaban use and permanent discontinuation on the rate of recurrent symptomatic VTE; to assess the rates of patient-relevant safety outcomes, including bleeding, ischaemic/haemorrhagic stroke, systemic embolic events (SEE), post-thrombotic syndrome (PTS), death, and hospitalisation due to cardiovascular causes; and to characterise the extent of adherence to edoxaban, reasons for and rate of discontinuation. To evaluate the effectiveness and safety of edoxaban relative to other anticoagulants, primary and secondary ETNA-VTE outcome data will be appraised in the context of those from the PREFER in VTE real-world registry and Hokusai-VTE clinical trial [12, 13]. The influence of study setting will also be explored by considering real-world ETNA-VTE data in the context of edoxaban data from the Hokusai-VTE clinical trial [12].

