### Sample size calculations

Assuming an overall 18-month symptomatic VTE recurrence rate [12, 13] of 8.0% in patients who receive edoxaban (regardless of treatment discontinuation) and a relative precision of 15% for a two-sided 95% confidence interval (95% CI), data for 1964 patients will be required to assess with sufficient accuracy the primary outcome. Given an expected dropout rate of 25%, enrolment of 2700 patients should result in an adequate sample size for evaluation at 18 months.

In order to obtain a dataset as large as possible for co-primary outcome assessment, safety data from ETNA-VTE-Europe will be combined with 18-month safety data from ETNA-AF-Europe, a sister European PASS study of edoxaban in approximately 13,100 patients with NVAF [10]. Together, these studies will enrol approximately 15,800 patients, with an overall expected 18-month dropout rate of 20%. Consequently, data for approximately 12,640 patients should be available at 18 months to assess the incidence rates of interest and their 95% CIs. A key aim of this combined analysis is to provide sufficient statistical power to capture uncommon ADRs with low incidence rates; for those that occur at rates of 0.1–1.0%, the corresponding precision of 95% CIs will range from ±0.06% to 0.17%.

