Data will be analysed and presented using descriptive statistics. Categorical variables will be reported as absolute numbers and percentages, and continuous variables will be presented as means with standard deviations or medians with interquartile ranges and minimum/maximum values, alongside the number of missing and non-missing observations. For select variables, 95% CIs will be provided. Where applicable, Kaplan-Meier analysis will be performed to illustrate risk over time. Time-to-event variables will be analysed using Cox proportional hazard regression and presented as hazard ratios with 95% CIs and *p*-values. The type of VTE (DVT only vs. PE ± DVT) will be included in all Cox models as an additional covariate. Based on the results of the Hokusai-VTE and the PREFER in VTE studies [6, 13], no further confounders will be considered at this stage, but any other relevant differences at baseline will be retrospectively added to the model.

A separate analysis combining 18-month safety data from ETNA-VTE-Europe and ETNA-AF-Europe will address the co-primary objective. Data will be presented as absolute and relative frequencies with 95% CIs, overall and for each aforementioned exposure category and subgroup. All statistical analyses will be performed using SAS® version 9.3 or higher (SAS Institute, Cary, NC, USA).

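### The pooled AF and VTE co-primary safety analysis lists exposure categories and subgroups as layers but not indication, so its rows can differ through AF/VTE mix alone

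*Protocol article*

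**What the plan says.** The Objectives and outcome measures section sets the co-primary target as edoxaban patients in both approved indications and defines the measure by counting patients in the two studies: "The outcome measure will be the proportion of patients who experience death (all-cause, cardiovascular, and VTE-related"), together with bleeding, hepatic events and other ADRs.

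The Statistical analysis section gives the co-primary objective its own analysis, "A separate analysis combining 18-month safety data from ETNA-VTE-Europe and ETNA-AF-Europe will address the co-primary objective", and fixes the presentation: "Data will be presented as absolute and relative frequencies with 95% CIs, overall and for each aforementioned exposure category and subgroup". The categories and subgroups referred to are those listed earlier in that section for the VTE registry:
- current, recent, past and last-30-day use;
- renal impairment and hepatic impairment;
- DVT only versus PE with or without DVT;
- age 75 and over, and sex;
- initial 30 mg versus 60 mg;
- active cancer.

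AF versus VTE is not on the list, and no weighting or adjustment by study is described.

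The Sample size calculations section gives the numbers. The AF study is "a sister European PASS study of edoxaban in approximately 13,100 patients with NVAF". It then says "Together, these studies will enrol approximately 15,800 patients, with an overall expected 18-month dropout rate of 20"%, so that "data for approximately 12,640 patients should be available at 18 months". The pooled precision for ADRs at rates of 0.1% to 1.0% is put at ±0.06% to 0.17%. For the VTE registry alone the section assumes a higher dropout: "Given an expected dropout rate of 25%, enrolment of 2700 patients should result in an adequate sample size".

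**The concern.** The clearest difference between the two merged cohorts is the reason for anticoagulation, and the pooled presentation does not show it. The list of layers appears to be carried over unadapted from the VTE registry: one entry, DVT only versus PE, is a classification of the index VTE and has no meaning for an AF patient.

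Two things are at stake.

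1. The overall frequency of an ADR is mainly an AF result. If the VTE frequency differs, the pooled figure will not reveal it, and its narrow interval may be read as applying to VTE patients. The same holds for VTE-related death, whose denominator would be mostly AF patients.
2. Readers will compare the exposure-category and subgroup rows with one another. The Background section says anticoagulation after VTE may last from 3 months to indefinitely, and the Potential limitations section concedes that varying exposure length may hamper interpretation. If VTE patients stop edoxaban more often than AF patients, the past-use row holds relatively more VTE patients than the current-use row. A difference between those rows could then reflect indication and not exposure. Age and starting dose raise the same problem if they are distributed differently in the two cohorts.

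**Working it through.** **Inputs from the article.** AF 13,100; VTE 2,700; combined dropout 20%; VTE dropout 25%; ADR rates 0.1% to 1.0%. Event rates by indication and the exposure mix by indication are not given, so they are assumed below.

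**1. The plan's own figures reproduce.**
- 13,100 + 2,700 = 15,800, and 15,800 × 0.80 = 12,640.
- Half-width = 1.96 × √(p(1−p)/n). With n = 12,640 this is 0.055% at p = 0.1% and 0.173% at p = 1.0%, which round to the stated 0.06% and 0.17%.

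**2. Weight of AF in the overall figure.**
- At enrolment: 13,100/15,800 = 82.9%.
- Among patients with 18-month data: VTE 2,700 × 0.75 = 2,025, AF 12,640 − 2,025 = 10,615, and 10,615/12,640 = 84.0%.
- Pooled frequency = 0.829 × AF rate + 0.171 × VTE rate. With assumed rates of 1% (AF) and 2% (VTE) it is 1.17%; with 1% and 3% it is 1.34%.

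**3. Precision by indication** (same formula).

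| Set | n | p = 0.1% | p = 1.0% |
|---|---|---|---|
| Pooled | 12,640 | ±0.06% | ±0.17% |
| AF | 10,615 | ±0.06% | ±0.19% |
| VTE, 25% dropout | 2,025 | ±0.14% | ±0.43% |
| VTE, 20% dropout | 2,160 | ±0.13% | ±0.42% |

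The VTE interval is √(12,640/2,025) ≈ 2.5 times as wide as the pooled one.

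**4. Spurious difference between exposure rows.** Assume no exposure effect within either indication and 20% of AF patients in past use; vary the share of VTE patients in past use.

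| VTE in past use | AF share, past use | AF share, the rest | Crude ratio past/rest, VTE rate twice AF | Same, VTE rate half AF |
|---|---|---|---|---|
| 20% | 83% | 83% | 1.00 | 1.00 |
| 40% | 71% | 87% | 1.14 | 0.92 |
| 60% | 62% | 91% | 1.26 | 0.85 |
| 80% | 55% | 95% | 1.38 | 0.79 |

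Last row worked, with the AF rate set to 1 and the VTE rate to 2: past use 0.548 × 1 + 0.452 × 2 = 1.452; the rest 0.951 × 1 + 0.049 × 2 = 1.049; ratio 1.38.

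A person-time version gives a similar range. Assume 1.35 years on and 0.15 off drug in AF, and 0.8 on and 0.7 off in VTE. Current-use person-years are 13,100 × 1.35 = 17,685 (AF) and 2,700 × 0.8 = 2,160 (VTE); past-use person-years are 1,965 and 1,890.
- Relative rates AF 4, VTE 2: past (1,965 × 4 + 1,890 × 2)/3,855 = 3.02; current (17,685 × 4 + 2,160 × 2)/19,845 = 3.78; ratio 0.80.
- Relative rates AF 2, VTE 4: past 2.98; current 2.22; ratio 1.34.

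If either the event rates or the exposure mix are equal across indications, the ratio is 1.00.

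**The case against.** The strongest reply is that the pooling is deliberate. The declared target is both indications together and the stated aim is precision for uncommon ADRs. All analysis is called explorative and descriptive, and the full protocol or SAP, not shown, may add columns by study. For the pooled set the article promises only that frequencies will be presented; the explicit comparisons of exposure categories are described for the VTE registry's own data. All this is fair and limits the point. It does not remove it: the article goes beyond silence and names the layers of the co-primary presentation, one of which cannot work for AF patients. Rows set side by side will be compared even without a ratio or a test.

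A reader might also infer stronger points that the article does not support.

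- **That the overall pooled frequency is confounded.** It contains no comparison. It is a weighted average for the declared population; it can hide heterogeneity, which is a weaker fault.
- **That the stated precision is wrong.** It is tied to the combined 12,640 patients and reproduces.
- **That VTE-specific safety results are lost.** The secondary objectives cover bleeding, stroke, death and other events in the VTE registry, and its safety data are to be shown Europe-wide, by country and by region. The gap is clearest for hepatic events and other ADRs, which the objectives name only under the pooled analysis, although Table 3 lists both among the registry's key outcome measures.
- **That the pooled interval will exclude both indications' rates.** This can be produced with 1.5% in AF and 3.0% in VTE (pooled 1.76% ± 0.23), but that lies outside the planned 0.1% to 1.0% range. With 0.5% and 1.0% the pooled result is 0.585% ± 0.133, which contains the AF rate though not the VTE rate.
- **That pooled rows will reverse the within-indication result.** A true ratio of 1.2 would appear as 1.2 × 0.80 = 0.96 in one assumed scenario. That shows possibility, not likelihood.

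**Conclusion.** The point holds as a flaw in how the co-primary presentation is laid out; there is no arithmetic error. Indication is missing from the stated layers although AF makes up 83% of enrolment, and the DVT/PE subgroup is carried into a population to which it mostly cannot apply. The overall pooled frequency is legitimate for its declared target. The exposure-category and subgroup rows are where a misleading reading can arise, and only if both event risk and row composition differ by indication. The article gives neither, so the ratios of about 0.8 to 1.4 illustrate what is possible under assumed twofold rate differences and unequal time on drug; they are not estimates. The precision result is firmer: it uses the article's own enrolment and dropout figures, and for VTE patients alone the half-width is about ±0.14% to ±0.43%.

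**What to change.** - Keep the pooled frequency for uncommon ADRs, and show each co-primary result by indication next to it, above all hepatic events and other ADRs.
- Stratify the pooled exposure-category and subgroup presentations by study.
- Restrict the DVT-only versus PE subgroup to VTE patients.
- In the sample size section, leave the pooled ±0.06% to 0.17% as it is and add the VTE-only precision of about ±0.14% to ±0.43% (n about 2,025).

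Study membership is known for every patient, so no new data are needed. The cost is more table columns and a VTE-only precision that looks less favourable than the pooled one.

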## Discussion

The real-world management of acute VTE has been studied by a number of registries on a national (MASTER and SWIVTER II [18, 19]), European (PREFER in VTE [13]) and global (RIETE, GARFIELD-VTE, RE-COVERY and XALIA [20–23]) scale. Such registries are important because they include patients who are usually omitted from clinical trials due to strict inclusion and exclusion criteria, allowing appraisal of treatment regimes in patients with particular characteristics. Furthermore, large-scale, non-interventional studies permit real-world comparisons across a range of healthcare settings and geographical locations, which may be helpful for evaluating the relative efficiency of national healthcare services and identifying potential improvement strategies. In this sense, ETNA-VTE Europe is similar to existing registries; however, it is different in that it focuses on patients receiving edoxaban, a drug that more recently been approved and is therefore not represented in previous real-world studies. The EMA has reviewed and approved its study protocol. Accordingly, the present registry will add value by providing an as-yet-unexplored insight into the use and associated outcomes of this agent in clinical practice. A comparison between the design of ETNA-VTE Europe and other large-scale VTE-patient registries can be found in Table 3.

**Table 3 Tab3:** Differences in design between ETNA-VTE Europe and other important European and global observational acute VTE registries

	Study design	Geographical scope	Patients	Agents of interest	Primary objective	Enrolment period	Key outcome measures	Status
ETNA-VTE Europe	Prospective, **single-arm**, observational PASS; **18-M FU**	310 sites across 8 European countries	2700 **edoxaban-treated** acute DVT and/or PE in/outpatients across multiple healthcare settings	**Edoxaban**	To **quantify the real-world, long-term rate of VTE recurrence in patients prescribed edoxaban** as part of acute VTE treatment	**Q4 2016**^**a**^ – **Q4 2018**	Mortality, recurrent VTE, bleeding events, **hepatic events,** ADRs, hospitalisation for CV causes**, edoxaban adherence/discontinuation**	O
RIETE [21]	Prospective, observational study; **3-M FU**	192 sites across 19 countries worldwide (**78% of data from weSpain**)	6855 acute DVT and/or PE in/outpatients across a range of healthcare settings	**Standard therapy (pre-DOACs)**	To improve physician knowledge of the natural history of thromboembolic disease and **develop scores to identify patients at high risk of complications**	**March 2001 – Feb 2004**	Mortality, recurrent VTE, bleeding events	C
XALIA [22, 24]	Prospective, observational PASS; **12-M FU**	Multiple sites^b^in 21 countries **worldwide**	5142 **acute DVT (±PE)** patients at hospitals or community care centres	**Rivaroxaban and standard therapy**	To assess the **safety and effectiveness of rivaroxaban** for the treatment of symptomatic DVT	**June 2012 – March 2014**	Mortality, recurrent VTE, bleeding events, CV events, treatment satisfaction/adherence/discontinuation, healthcare resource utilisation, TEAEs	C
PREFER in VTE [13, 14]	Prospective, observational study; **12-M FU**	381 sites across 7 European countries	3455 acute DVT and/or PE in/outpatients across a range of healthcare settings	**DOACs (pre-edoxaban)**	To explore patient characteristics, VTE management strategies, **healthcare resource usage and associated costs**	**Jan 2013 – Jan 2014**	Mortality, recurrent VTE, bleeding events, MI, stroke, SE, post- thrombotic syndrome, CV events	C
GARFIELD-VTE [20, 25]	Prospective, observational study; **two sequential cohorts; 3-Y FU**	415 sites across 28 countries **worldwide**	10,878 acute DVT and/or PE in/outpatients across a range of healthcare settings	**Standard therapy and DOACs**	To identify **regional/temporal treatment variations** and **assess their impact on** clinical/**economic** outcomes	**July 2014 – Sept 2016**	Mortality, recurrent VTE, bleeding events, post-thrombotic syndrome, chronic thromboembolic pulmonary hypertension, healthcare resource utilisation	O
RE-COVERY [23, 26]	Prospective, observational PASS; **12-M FU**	~17^b^ sites in 5 countries **worldwide**	~ 8000 acute DVT and/or PE patients	**Dabigatran and VKA**	To characterise the VTE patient population and **compare the safety and effectiveness of dabigatran to VKA**	Nov 2015 – Dec 2018	Mortality, recurrent VTE, bleeding events	O

*Legend*: Y, year; M, month; DVT, deep vein thrombosis; FU, follow-up; PE, pulmonary embolism; DOAC, direct oral anticoagulant; VTE, venous thromboembolism; TIA, transient ischaemic attack; PASS, post-authorisation safety study; Q4, fourth quarter; MI, myocardial infarction; SE, systemic embolism; CV, cardiovascular; VKA, vitamin-K antagonist, C, completed; O, ongoing, TEAE, treatment-emergent adverse events. Important differences are highlighted in **bold**. ^a^Swiss sites: February 2015. ^b^Precise number unknown

Current evidence for the safety and efficacy of edoxaban largely emanates from the phase III Hokusai-VTE clinical trial [6]. A key limitation of this study was the exclusion of patients with characteristics encountered in routine clinical practice, such as those with isolated distal symptomatic DVT, a creatinine clearance of < 30 mL/min, and significant liver disease. Consequently, the effectiveness and safety in some clinical subgroups to edoxaban remain unrepresented and uncharacterised. Data gathered from the ETNA-VTE-Europe study with minimal selection criteria will address this knowledge gap, with several pertinent subgroup analyses already planned. The gathered data will also provide a snapshot of the types of patients being prescribed edoxaban, the doses used, and the durations of treatment in a real-life setting. This will permit appraisal of the appropriateness of such therapeutic decisions as well as acting as a marker for evaluation of subsequent trends of prescription.

An additional limitation of current studies is that data are only available for up to 12 months of edoxaban therapy [6]. Considering that a number of patients will require longer-term anticoagulation in clinical practice [8], those continuing edoxaban dosing beyond 12 months will find themselves in uncharted waters. The 18-month follow-up period planned for ETNA-VTE-Europe patients will provide clinicians and patients with valuable information regarding the safety and net clinical benefit of extended treatment. In particular, trends in rare ADRs such as liver events and major bleeding will be of interest, given their low frequency in the Hokusai-VTE trial [6]. Combination of ETNA-VTE-Europe data with those from the ETNA-AF-Europe sister study will provide an even larger population from which to assess these safety outcomes [10]. Thus, the present PASS is a responsible and important part of the early post-marketing phase, designed to address several of the knowledge gaps highlighted in the EMA risk-management plan for edoxaban [9].

The single-arm design of the ETNA-VTE-Europe study reflects its key aim of characterising the real-world safety and effectiveness of edoxaban. However, visually comparing our results to those from similar studies with different anticoagulants will help to provide perspective. To these ends, data from the recent PREFER in VTE real-world registry will be used to contextualise data from ETNA-VTE-Europe, selected for its comparable bleeding definitions, coinciding data assessment time points, and high patient numbers (3545 patients) [14]. This will allow us to gain an idea of the real-world safety and effectiveness of edoxaban relative to agents such as VKAs and other DOACs, not only in the overall population, but also in specific patient subsets, such as those with renal or hepatic impairment. Furthermore, several of the countries and regional delineations in ETNA-VTE-Europe (such as Italy, DACH and UK/IE) also feature in the PREFER in VTE study, enabling various approximate geographical comparisons [13]. A further evaluation of ETNA-VTE-Europe real-world results in the context of those from the Hokusai-VTE clinical trial will provide insight into the influence of stringent enrolment criteria and closer monitoring on edoxaban-related outcomes. This will indicate to what extent the encouraging findings from phase III studies can be expected to translate into clinical practice.

### Potential limitations

As a prospective, non-interventional registry that aims to represent everyday occurrence and management of VTE, the stringent inclusion/exclusion criteria, physician/patient blinding, and site/protocol standardisation that typify RTCs do not apply. This introduces the possibility for biases that are difficult to avoid, measure or correct for. In particular, heterogeneous timing and length of edoxaban exposure may prove problematic for the interpretation of results, thought this will be taken into consideration at data analysis. Furthermore, in such a large-scale study, some incompleteness, insufficient detail, or inaccuracy of patient data is unavoidable; however, measures such as the careful design of case report forms and data monitoring/verification aim to minimise such occurrences. Despite the inherent limitations associated with observational registries, the all-inclusive nature of ETNA-VTE Europe may be seen as an advantage for obtaining a realistic snapshot of the clinical climate, with two-wave recruitment potentially allowing changes in treatment behaviour over time to be elucidated. Finally, while the single-arm nature of the study means that direct comparisons with other anticoagulants will not be possible, close accordance between the designs of PREFER in VTE and ETNA-VTE Europe should permit a reasonable appraisal of outcome differences.

